### Therapeutic decision making

In this study, “metastatic tumor” is defined as histologically diagnosed lesions in permanent specimens regardless of the positive or negative detection using NIR-ICG imaging. Local treatment (surgery or radiotherapy) is cancelled for patients with metastatic tumor or positive PWC who are diagnosed using staging laparoscopy (Fig. 1).

**Fig. 1 Fig1:**
[figure not shown]
Therapeutic decision making by staging laparoscopy. SL: staging laparoscopy; PWC: peritoneal washing cytology

### Schedule

The flowchart of this study is shown in Fig. 2. Table 1 shows the schedule for the observations, tests, and assessments, which will be performed by the principal investigator or sub-investigators. There are no relevant restrictions regarding concomitant care or interventions that are prohibited during the trial. Patients may withdraw or be withdrawn from the study at any time, at which point the date of discontinuation, reason for discontinuation, clinical course, and safety and efficacy outcomes will be recorded in the patient’s medical record and case report form (CRF). The withdrawal criteria are:
The patient wishes to withdraw from the study or withdraws their informed consent.The patient is found to be ineligible after their registration.Exacerbation of complications (e.g., previous disease) precludes further testing or evaluation.The patient is found to be pregnant.The study is terminated.

**Fig. 2 Fig2:**
[figure not shown]
Flowchart for this study. PDAC: pancreatic ductal adenocarcinoma; SL: staging laparoscopy; PWC: peritoneal washing cytology

**Table 1 Tab1:** Study steps and evaluations

	Study period			
	Enrolment	Intervention (staging laparoscopy)	Post-intervention	
			7 days	12 months
Informed consent	○			
Physical examination	○	○	○	○
Demographics and medical history	○			
Blood testing	○	○	○	○
Abdominal CECT	○			○
EOB-MRI	○			
FDG-PET	○			
Administration of ICG		○		
Adverse events		○	○	○
PDAC recurrence			○	○

*CECT* contrast-enhanced computed tomography, *EOB-MRI* gadolinium ethoxybenzyl diethylenetriamine pentaacetic acid-enhanced magnetic resonance imaging, *FDG-PET* 18F-flurodeoxyglucose positron emission tomography, *ICG* indocyanine green, *PDAC* pancreatic ductal adenocarcinoma

### Data collection

The principal investigator or sub-investigators will complete the CRFs, and the data manager will collect the CRFs to construct datasets for the statistical analysis. Safety information will be recorded as a secondary endpoint on the CRF, and severe cases will be reported to the ethical committee within 30 days.

A list of subject identification codes will be prepared to link the participants’ records to the records in the study database. The subject identification codes will also be used at the participants’ enrollment and on their CRFs. Limited information, such as sex and date of birth, may be used to identify the subjects or verify the list of subject identification codes, in accordance with all applicable laws and regulations. Finally, the participants’ data will be de-identified by the principal investigator or sub-investigators, and the data management will subsequently rely on the subject identification codes, which will not be shared with any outside parties. All study-related publications will be created in a format that prevents the participants from being personally identified.

### Analysis methods

#### Analysis population

The analysis dataset will include data from all enrolled participants who completed the staging laparoscopy, but without data from patients who withdrew their informed consent or did not complete the NIR-ICG imaging for any reason.

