### Staging laparoscopy (intervention)

Enrolled patients will receive ICG intravenously (0.5 mg/kg) on the day before staging laparoscopy. During staging laparoscopy, peritoneal washing cytology (PWC) sample from the pelvis with 100 ml of normal saline is collected at first. The abdominal cavity will be observed using standard white-light laparoscopic imaging and then using NIR-ICG imaging. Suspicious lesions that are defined as detectable nodules under white-light imaging or NIR-ICG imaging on the liver or peritoneum, will be examined intraoperatively using frozen sections and permanent specimens. If more than five suspicious lesions are observed on the individual organs (liver and peritoneum), we will examine five lesions using frozen sections for each organ, and additional specimens of the frozen sections will be taken when all specimens are diagnosed as benign lesions in the first examination. We will resect up to ten lesions for each organ.

The findings will be evaluated intraoperatively by the entire operative team (two or three surgeons) and at least one other surgeon will postoperatively review the recorded video. We have defined the benefit of NIR-ICG imaging as the identification of additional liver or peritoneal lesions that were not identified during the standard white-light imaging. The final judgement will be based on consensus among the operative surgeons.

Each lesion that was taken during staging laparoscopy is examined using standard white-light imaging, NIR-ICG imaging, and histological finding to detect for positive or negative lesions. False positive or negative detection with white-light imaging and NIR-ICG imaging is recorded according to the confirmed findings of staging laparoscopy and histological diagnosis.

The staging laparoscopy will be performed using a laparoscopic high-definition fluorescence imaging system (Karl Storz GmbH & Co. KG, Tuttlingen, Germany). The system includes light sources for white-light and 760-nm light, as well as a 30° 10-mm laparoscope containing optical filters. The system allows the surgeon to easily switch between the white-light and NIR sources using a foot pedal.

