#### *Statistical analysi*s

The subjects’ baseline characteristics will be reported using summary statistics and distributions. Nominal variables will be reported as number and proportion. Continuous variables will be reported as the number of subjects, mean and standard deviation values, as well as minimum, median, and maximum values. The primary outcome analysis will evaluate the proportion and 95% confidence interval for the identification of at least one additional metastatic tumor using NIR-ICG imaging. The hypothesis testing will be based on a single sample, a null hypothesis of 0% efficacy, and a one-sided significance level of 2.5%. Efficacy is defined as the identification of at least one metastatic tumor that was not detected using standard white-light imaging. “Metastatic tumor” is defined as a histologically diagnosed lesion with adenocarcinoma. The sensitivity and specificity of white-light imaging and NIR-ICG imaging will be investigated. Safety outcomes will be evaluated using the proportion and two-sided 95% confidence interval based on a binomial distribution.

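### Safety is analysed only in patients who completed laparoscopy and NIR imaging, so a patient whose procedure is abandoned after an ICG reaction drops out of the safety proportion

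*Protocol article*

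**What the plan says.** The Analysis population section of the protocol article defines a single dataset: "The analysis dataset will include data from all enrolled participants who completed the staging laparoscopy". Two groups are then taken out of it. One is those who took back their consent; the other is anyone who "did not complete the NIR-ICG imaging for any reason". No second set is defined for any outcome.

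The Statistical analysis section, which follows directly, covers both the primary outcome and safety. On safety it says: "Safety outcomes will be evaluated using the proportion and two-sided 95% confidence interval based on a binomial distribution". It attaches no other population to that sentence. The Data collection section gives safety formal standing: "Safety information will be recorded as a secondary endpoint on the CRF".

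On timing, the Staging laparoscopy section states: "Enrolled patients will receive ICG intravenously (0.5 mg/kg) on the day before staging laparoscopy".

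The Schedule section says that when a patient is withdrawn, the safety and efficacy outcomes are still entered in the medical record and the CRF. Table 1 lists adverse events at the intervention, at 7 days and at 12 months.

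**The concern.** A safety denominator should be fixed by exposure. Here it is fixed by two things that happen after exposure: finishing the laparoscopy and finishing the NIR imaging. Either can fail because of the very event that the safety analysis is meant to count. A patient who reacts to ICG, and whose laparoscopy is then cancelled or cut short, meets the exclusion rule.

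At stake is the one numerical safety statement the study plans to make. With about 40 patients and few expected events, moving a single event in or out decides whether the report shows none or some.

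**Working it through.** **Order of events.** ICG on the day before; laparoscopy started; white-light inspection; NIR inspection; laparoscopy completed. The inclusion conditions are judged at the end of this chain, while exposure is at its start.

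**When the rule biases the proportion.** Let N be the patients given ICG, D those among them who did not complete, x the events among completers and r the events among the D.

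- As planned: x / (N − D).
- All exposed: (x + r) / N.

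The second is a weighted average of x / (N − D) and r / D. The planned figure is therefore too low whenever r / D exceeds x / (N − D), which is what to expect if events cause non-completion. If non-completion is unrelated to events, the rule loses information but does not bias the figure.

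**The plan's own counts.** From the Sample size section: 7 / 0.2 = 35, and 35 + 5 dropouts = 40. Both reproduce. The protocol gives no expected rate of ICG reactions and does not say how many dropouts would already have been dosed, so what follows is illustration.

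**Illustration for safety.** Assume all 5 dropouts received ICG and did not complete, and that one of them had the only reaction (N = 40, D = 5, x = 0, r = 1). Exact (Clopper-Pearson) two-sided 95% intervals:

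- As planned: 0/35 = 0%. Lower limit 0; upper limit 1 − 0.025^(1/35) = 10.0%.
- All exposed: 1/40 = 2.5%. Lower limit 1 − 0.975^(1/40) = 0.06%; upper limit, the 97.5% quantile of Beta(2, 39), = 13.2%.

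**Range around it.** The planned figure is 0/35 in each row.

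| Assumption about the 5 dropouts | All exposed | 95% CI |
|---|---|---|
| Only one was dosed, and that one reacted | 1/36 = 2.8% | 0.07 to 14.5% |
| All five dosed, one reacted | 1/40 = 2.5% | 0.06 to 13.2% |
| All five dosed, all five reacted (extreme) | 5/40 = 12.5% | 4.2 to 26.8% |

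**Efficacy under the same rule.** Assume all 5 were dosed and started laparoscopy, and that there were 4 detections among the 35 completers.

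- Completers: 4/35 = 11.4% (3.2 to 26.7%).
- If none of the 5 had a detection: 4/40 = 10.0% (2.8 to 23.7%). The completer figure is higher by a factor of 40/35 = 1.14.
- If one of the 5 already had a confirmed NIR-only metastasis before imaging stopped: 5/40 = 12.5% (4.2 to 26.8%). The completer figure is now the lower one.

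So the direction of the efficacy effect is not fixed by the rule.

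**The case against.** The strongest reply is that no safety information is lost. Outcomes of withdrawn patients are recorded, and severe cases go to the ethics committee. That stands for collection and reporting of events. It does not cover the planned proportion and interval, which are computed on a dataset that leaves these patients out.

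A second reply is that a condensed article leaves a separate safety set to the full protocol or SAP, and that the article never says in so many words that its dataset serves every outcome. The second part is true. But the article does more than stay silent: it states an explicit exclusion rule for the analysis dataset and follows it with a safety analysis that has no other denominator. A wider safety set elsewhere would have to override that rule.

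Third, the withdrawal criterion closest to this situation ("Exacerbation of complications (e.g., previous disease) precludes further testing or evaluation") gives previous disease as its example and does not mention ICG reactions. That is fair. The criterion shows that withdrawal on medical grounds is foreseen, not that it will be due to ICG.

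A reader might go further and infer that the rule also inflates the NIR yield by conditioning on a test that worked. The protocol does not support this as a general claim:

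- An NIR inspection that is carried out and shows nothing is a completed examination, so it stays in the denominator as a negative result.
- Nothing in the protocol lets the team stop NIR imaging because white light has already shown gross disease.
- Analysing evaluable patients only is a defensible choice in a study that calls itself exploratory and plans for 35 patients plus 5 dropouts.
- Against a null of 0%, any single detection contradicts the null. Removing patients without a detection therefore does not change the test decision.

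**Conclusion.** The safety part holds. As written, the safety proportion is restricted to patients who completed both laparoscopy and NIR imaging, although exposure precedes both. It can therefore be biased downward, and is so when adverse events after ICG cause non-completion. In the illustration it reads 0/35 where the figure among all exposed is 1/40. That comparison assumes that all 5 possible dropouts had been dosed and that there were no other events. The Sample size section says neither, and some dropouts, such as patients found ineligible after registration, could leave before dosing. So 1/40 should not be read as the correct figure, only as what one lost event would look like.

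For efficacy, the protocol does not establish that the yield is overstated. With 5 of 40 removed, the effect is modest and may run either way. A sensitivity analysis is enough.

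**What to change.** 1. Define a safety set of every patient who received any ICG, whether or not laparoscopy or NIR imaging was completed, and compute the safety proportion and interval in it. If a patient who withdrew consent also refused use of data already collected, state that count separately.
2. Keep the completer set for the primary outcome if wished. Add a sensitivity analysis in all dosed patients who started laparoscopy. Count incomplete NIR imaging as no additional detection unless a histologically confirmed metastasis seen only with NIR had already been found. Such a patient meets the Primary outcome definition and must not be scored as a failure.
3. Tabulate the number of non-completions and their reasons, separating those before dosing from those after.

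The cost is wording and one extra table. The sample size does not change and no new data are needed, since the Schedule section and Table 1 already provide for recording safety outcomes and adverse events. The only downside is that the reported safety figure may be less favourable.

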#### *Statistical analysi*s

The subjects’ baseline characteristics will be reported using summary statistics and distributions. Nominal variables will be reported as number and proportion. Continuous variables will be reported as the number of subjects, mean and standard deviation values, as well as minimum, median, and maximum values. The primary outcome analysis will evaluate the proportion and 95% confidence interval for the identification of at least one additional metastatic tumor using NIR-ICG imaging. The hypothesis testing will be based on a single sample, a null hypothesis of 0% efficacy, and a one-sided significance level of 2.5%. Efficacy is defined as the identification of at least one metastatic tumor that was not detected using standard white-light imaging. “Metastatic tumor” is defined as a histologically diagnosed lesion with adenocarcinoma. The sensitivity and specificity of white-light imaging and NIR-ICG imaging will be investigated. Safety outcomes will be evaluated using the proportion and two-sided 95% confidence interval based on a binomial distribution.

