### Sample size

The target sample size is set to 40 patients in order to detect a significant difference in the primary outcome. Studies of NIR-ICG imaging for colorectal cancer have indicated that 10–43% of patients had additional metastases that were only identified using NIR-ICG imaging [7]. Thus, we conservatively assumed that NIR-ICG imaging would detect additional radiographically occult metastases in 10% of the cases. Thus, 7 patients would be needed to identify a significant difference in the primary outcome, based on a null hypothesis of 0% efficacy with a one-sided significance level of 2.5 and 80% power. Between April 2014 and June 2016, we retrospectively determined that the expected rate of radiographically occult PDAC metastases was approximately 20% at our center (26% of 72 historically study-eligible patients). Therefore, we calculated the required sample size to be 35 patients (7 / 0.2 = 35), and increased the sample size to 40 patients to account for 5 possible dropouts. Kobe University Hospital typically treats 20–30 patients per year who would be considered eligible for the study, which suggest that a sufficient number of patients may be enrolled during the recruitment period.

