Imaging using NRI-ICG can contribute to R0 resection of hepatocellular carcinoma and colorectal metastasis to the liver, with a high detection rate for hepatic lesions [10, 11]. Peritoneal metastasis can also be identified using NIR-ICG imaging [4], and several other studies have indicated that NIR-ICG imaging is useful in patients with PDAC or periampullary malignancies. For example, Handgraaf et al. reported that NIR-ICG imaging provided additional value based on its high negative predictive value in cases of pancreatic cancer [12], while Yokogawa et al. and Katada et al. reported detection rates of 16 and 15% for using NIR-ICG imaging to detect unsuspected metastasis from pancreatic cancer [13, 14]. Nevertheless, there are scarce data regarding the role of NIR-ICG imaging for staging PDAC. Therefore, the present study aims to establish the clinical utility of NIR-ICG imaging for identifying occult metastases in radiographically non-metastatic PDAC. If the efficacy of this approach is confirmed, this modality may help physicians and patients avoid needless major surgery or radiotherapy.

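### The primary test of a 0% null is degenerate: one success rejects it, the 2.5% level plays no part, and a significant result shows only that the yield is not exactly zero

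*Protocol article*

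**What the plan says.** The Statistical analysis section gives the proportion and 95% confidence interval for the primary outcome, without naming the interval method, and adds a test: "The hypothesis testing will be based on a single sample, a null hypothesis of 0% efficacy, and a one-sided significance level of 2.5" (per cent). The unit of success is the patient: "Efficacy is defined as the identification of at least one metastatic tumor that was not detected using standard white-light imaging", with adenocarcinoma confirmed histologically. The denominator (Analysis population) is every enrolled patient who completed staging laparoscopy and NIR-ICG imaging, apart from withdrawals of consent.

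The Sample size section uses the same null. Its stated purpose is that "The target sample size is set to 40 patients in order to detect a significant difference in the primary outcome". For the alternative, "we conservatively assumed that NIR-ICG imaging would detect additional radiographically occult metastases in 10% of the cases". It concludes that "7 patients would be needed to identify a significant difference in the primary outcome". The parameters behind that figure are the 0% null, a one-sided level of 2.5% and power of 80%. The 7 is divided by an occult-metastasis rate of about 20% to give 35, and 5 are added for dropouts.

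The article gives no minimum worthwhile rate, non-zero null or required number of successes. The Discussion ends with: "If the efficacy of this approach is confirmed, this modality may help physicians and patients avoid needless major surgery or radiotherapy".

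**The concern.** A significance test is useful when the null is a value the data could plausibly have come from and rejecting it means something for practice. A null of exactly 0% does neither. Under it the number of successes is 0 with certainty, so any success refutes it and there is no sampling distribution for the 2.5% level to act on. The test asks whether NIR-ICG can ever show a confirmed metastasis that white light missed, not whether it does so often enough to matter.

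At stake is how the primary result will be read. One positive patient in 40 could be reported as statistically significant efficacy although the data would be compatible with a negligible yield, and the Discussion links confirmed efficacy to avoiding surgery or radiotherapy. The same null supplies the trial's stated 80% power, so that figure is affected too.

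**Working it through.** **Inputs.** From Sample size and Statistical analysis: null p0 = 0, alternative p1 = 0.10, one-sided alpha = 0.025, power 0.80. From Sample size: base n = 7, occult-metastasis rate 0.2, 35 evaluable patients, 40 enrolled.

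**1. Reproducing the 7.** The one-sample normal approximation with the variance under the null is

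n = [z(1−alpha)·√(p0(1−p0)) + z(power)·√(p1(1−p1))]² / (p1 − p0)².

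With p0 = 0 the first term is z(1−alpha) × 0 = 0. The rest is (0.8416 × √(0.10 × 0.90))² / 0.10² = (0.8416 × 0.3)² / 0.01 = 6.37, rounded up to 7. Then 7/0.2 = 35 and 35 + 5 = 40, as stated. Because alpha is multiplied by zero, alpha = 0.0001, 0.025, 0.05 and 0.20 all give 7.

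The approximation also fails on power. Exactly, the chance of at least one success among 7 patients at a 10% rate is 1 − 0.9^7 = 52%. Reaching 80% takes ln 0.2 / ln 0.9 = 15.3, that is 16 patients.

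**2. The rejection rule.** Let X be the number of patients with a success. Under p = 0, P(X ≥ 1) = 1 − 1^n = 0. The exact rule is therefore to reject when X ≥ 1; its type I error is 0 and a single success gives p = 0. A z-test with the null variance would divide by √(0 × 1/n) = 0 and is undefined.

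**3. Chance of a significant result**, 1 − (1 − p)^n:

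| True rate among all analysed | n = 35 | n = 40 |
|---|---|---|
| 1% | 30% | 33% |
| 2% | 51% | 55% |
| 5% | 83% | 87% |
| 10% | 97.5% | 98.5% |

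The 2% row is the overall rate if the assumed 10% applies only within the 20% who have occult metastases, as the division by 0.2 implies (0.10 × 0.20). The 10% row applies if the 10% refers to all analysed patients.

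**4. What the intervals say at n = 40.**

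- Clopper-Pearson 95%: 0/40 gives 0 to 8.8%; 1/40 gives 0.06% to 13.2%; 4/40 gives 2.8% to 23.7%.
- Wald 95% for 1/40: 0.025 ± 1.96·√(0.025 × 0.975/40) = −2.3% to 7.3%. The Wald lower limit is −0.7% at 3/40 and first exceeds 0 at 4/40 (+0.7%).

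**5. Non-zero thresholds.** The minimum rates below are illustrative assumptions, since the article names none. The rule is exact at one-sided 2.5%, with power at a true rate of 10%.

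| Rate to exclude | Successes needed in 40 | Actual type I error | Power at n = 40 | n at which power first reaches 80% |
|---|---|---|---|---|
| 1% | 3 | 0.7% | 78% | 42 |
| 2% | 4 | 0.8% | 58% | 54 |
| 5% | 6 | 1.4% | 21% | 213 |

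**The case against.** Several points on the other side have weight.

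- **Error control is not lost.** A type I error of 0 is below 2.5%, and one histologically confirmed NIR-only lesion does refute a claim that such lesions never occur. A reader might infer that the test inflates false positives. It does not; the fault is that the null is uninformative.
- **The trial can fail.** A reader might infer that the trial is bound to succeed. That is nearly so if 10% or more of all analysed patients have an NIR-only metastasis, but at the 2% overall rate implied by 7/0.2 it would miss significance almost half the time.
- **The test statistic is not named.** A Wald-type test would need 4/40 to reject. However, the corresponding sample-size formula, with the variance under the alternative, gives 71 rather than 7, so the article's own figure points to the null-variance approach.
- **Test and interval need not conflict.** A reader might infer that the test contradicts the planned interval. That would happen only with a Wald interval; the exact interval excludes 0 at 1/40, in line with an exact test.
- **A second look is only a possibility.** White light always precedes NIR-ICG (Staging laparoscopy section), so some NIR-only finds could come from a repeated inspection rather than from the dye. The documents give no rate, so this is an assumption and not evidence against the null.
- **The study is described as exploratory** (Data monitoring and auditing), the proportion and interval are already planned, and the closing sentence of the Discussion is not a decision rule. This softens the consequence. It does not remove a formal test that is prespecified and used to size the trial.

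**Conclusion.** The point holds. The 0% null makes the primary test degenerate: under an exact test a single success rejects it, and the 2.5% level affects neither the test nor the base sample size. The stated 80% power rests on an approximation that fails here; at the base 7 patients and a 10% rate it is 52%. A significant result would establish only that the yield is not exactly zero, and 1/40 would qualify with an exact interval reaching down to 0.06%.

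The degeneracy depends on no assumed rate. The chance of significance does: about half at an overall rate of 2%, and nearly certain at 10%. The article does not settle which of these its 10% implies for all analysed patients. Since this is the primary analysis and the null is stated in the article itself, it is not a detail that can be left to a separate analysis plan.

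**What to change.** In the Sample size and Statistical analysis sections, delete the hypothesis test against 0% and the 80% power statement. Make the proportion with a Clopper-Pearson 95% confidence interval the primary analysis, and describe the study as estimation-based, which fits the exploratory label it already carries.

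Deleting the test removes the stated basis for 35 and 40 patients, so replace it with a precision statement for the existing 40. For example, 4/40 would give 2.8% to 23.7%, and 0/40 would give 0 to 8.8%.

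If a decision rule is wanted, prespecify a non-zero minimum rate that the lower exact limit must exceed, and report its power at 40 patients and a true rate of 10%: 78% to exclude 1%, 58% to exclude 2%, 21% to exclude 5%. The choice of rate belongs to the investigators, with these figures in view.

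Cost: the trial gives up an easily obtained significance claim and its stated 80% power. The study opened in March 2018, so the change needs a protocol amendment. Estimation alone needs no extra patients. A rule with 80% power would need more than 40 at any of the three rates shown.

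### Absolute lesion-level sensitivity and specificity cannot be estimated when only lesions flagged by white light or NIR-ICG receive histology

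*Protocol article*

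**What the plan says.** The protocol article, Statistical analysis, plans the accuracy analysis in one sentence: "The sensitivity and specificity of white-light imaging and NIR-ICG imaging will be investigated". It gives no unit of analysis and no denominator.

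The section Staging laparoscopy (intervention) fixes which lesions can enter that analysis:

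- Selection for histology: "Suspicious lesions that are defined as detectable nodules under white-light imaging or NIR-ICG imaging on the liver or peritoneum, will be examined intraoperatively".
- Limit on sampling: five lesions per organ are examined first, and more are taken only if all of those are benign. The ceiling is "We will resect up to ten lesions for each organ".
- Lesions classified: "Each lesion that was taken during staging laparoscopy is examined using standard white-light imaging, NIR-ICG imaging, and histological finding".
- Reference for errors: "False positive or negative detection with white-light imaging and NIR-ICG imaging is recorded according to the confirmed findings of staging laparoscopy", together with the histological diagnosis.

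Table 1 schedules contrast-enhanced CT at 12 months and records recurrence at 7 days and 12 months. No section links either to the accuracy analysis.

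**The concern.** Sensitivity needs the number of all metastases, including those that neither modality shows. Specificity needs the number of all benign lesions, including those that neither modality flags. The design observes neither group, because a lesion must be visible on at least one modality before it is biopsied.

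Missed disease is to be expected. The Discussion cites a meta-analysis in which 18% of patients with resectable disease were found unresectable at laparotomy despite staging laparoscopy. Not all of these need have been metastatic, and some might have been seen with NIR-ICG, but the figure shows that laparoscopy leaves disease undetected.

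At stake are figures that readers would carry forward as the accuracy of NIR-ICG. Each modality's figure would depend partly on the errors of the other.

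**Working it through.** The plan states no expected sensitivity or specificity, so there is no figure to reproduce. The structure comes from the Staging laparoscopy section; all rates and counts below are assumptions.

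**1. Sensitivity.** Among metastatic lesions let *a* be seen by both modalities, *b* by white light (WL) only, *c* by NIR-ICG only and *d* by neither. Only *a*, *b* and *c* reach histology.

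- True WL sensitivity = (a+b)/(a+b+c+d); reported = (a+b)/(a+b+c).
- True NIR sensitivity = (a+c)/(a+b+c+d); reported = (a+c)/(a+b+c).
- Each reported value is the true value divided by U, the share of metastases seen by at least one modality. Both are too high whenever d > 0.
- Sum of the reported values = 1 + a/(a+b+c), so at least 100% whatever the tests do.

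**2. Size for sensitivity.** With true sensitivities s₁ and s₂ and correlation ρ between detections, U = s₁ + s₂ − [s₁s₂ + ρ√(s₁(1−s₁)s₂(1−s₂))].

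For 60% and 70%:

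- Independent: U = 0.60 + 0.70 − 0.42 = 0.88. Reported: 0.60/0.88 = 68% and 0.70/0.88 = 80%.
- ρ = 0.5: U = 1.30 − (0.42 + 0.5 × √0.0504) = 0.768. Reported: 0.60/0.768 = 78% and 0.70/0.768 = 91%.

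| Assumed true WL / NIR | Reported, independent | Reported, ρ = 0.5 |
|---|---|---|
| 50% / 60% | 63% / 75% | 74% / 89% |
| 60% / 70% | 68% / 80% | 78% / 91% |
| 70% / 80% | 75% / 85% | 83% / 94% |
| 90% / 90% | 91% / 91% | 95% / 95% |

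The distortion is small if both modalities are very sensitive. It grows when they miss the same lesions.

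**3. The same in counts.** Assume 12 verified metastases: 6 seen by both, 2 by WL only, 4 by NIR only. Reported sensitivities are 8/12 = 67% and 10/12 = 83%. With 5 unseen metastases the true values are 8/17 = 47% and 10/17 = 59%; with 10 unseen, 8/22 = 36% and 10/22 = 45%. The trial's data would be identical in all three cases.

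**4. Specificity.** Among verified benign lesions let *e* be flagged by both, *f* by WL only and *g* by NIR only.

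- Reported WL specificity = g/(e+f+g); reported NIR specificity = f/(e+f+g).
- Sum = 1 − e/(e+f+g), so at most 100%. The two cannot both exceed 50%, however good the tests are.
- With the other counts fixed, more benign nodules flagged only by white light (larger *f*) raise NIR-ICG's reported specificity.

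**5. What can still be estimated.** The unseen cell cancels in ratios. The NIR-to-WL ratio of sensitivities is (a+c)/(a+b), with no *d* in it: 10/8 = 1.25 in the count example, and 0.70/0.60 = 0.80/0.68 = 1.17 (unrounded) in the rate example. The ratio of false-positive counts, (e+g)/(e+f), behaves in the same way. Each modality's positive predictive value also uses only lesions it flagged. All of these apply to lesions actually examined, so the five- and ten-lesion rules may still add selection. The article does not allow the direction of that selection to be determined.

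**The case against.** **The analysis is minor.** Sensitivity and specificity are neither the primary outcome nor a listed secondary one. They carry no hypothesis or sample-size role, and the section on data monitoring and auditing calls the study exploratory. This stands and limits the weight of the point. A reader might infer that the primary result is biased too. It is not: that outcome needs only a histologically proven metastasis that white light did not show, so lesions missed by both do not enter it.

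**The unit could be the patient.** Patients without any suspicious nodule would then be negative on both modalities, and the 100% limit on the specificities would not apply. For example, take 35 patients and the 26% historical rate of occult metastases: about 0.74 × 35 ≈ 26 would be metastasis-free. With an assumed 3 and 5 false-positive patients, the specificities are 23/26 = 88% and 21/26 = 81%. The limit is indeed specific to lesions. But the article scores errors on lesions taken, gives laparoscopy and histology as the reference, and assigns follow-up no role. The patients counted as negative would be unverified, so this reading does not rescue the planned figures.

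**The loss in specificity cannot be sized.** This stands. One could assume true specificities of 90% for both and derive a reported 47%, but that presupposes a countable population of benign lesions mostly invisible on both modalities. The article defines suspicious lesions as detectable nodules, so no such population exists in the plan. Only the algebraic limit is secure.

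**Clustering of lesions within patients.** The article fixes no interval or test for these figures. The choice can be left to the statistical analysis plan, and its absence here is no fault.

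**Conclusion.** The point holds for absolute, lesion-level sensitivity and specificity. With no histology on tissue negative on both modalities, neither can be estimated from the planned data, and no later choice of analysis method can fill the empty cell.

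The sensitivities are biased upwards whenever a metastasis is missed by both; the sizes above rest on assumed true rates and correlations, since the article gives none. The limit of 100% on the sum of the specificities needs no assumption beyond the sampling rule.

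A reader might go further and infer that the study can say nothing about comparative accuracy. The documents do not support that: positive predictive values and the ratios between modalities remain estimable among examined lesions. This is a point that should be fixed in a descriptive analysis, not a threat to the trial's main conclusion.

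**What to change.** Replace the sentence on sensitivity and specificity in the Statistical analysis section. Among histologically examined lesions, report:

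- each modality's positive predictive value;
- the NIR-to-white-light ratio of true-positive counts;
- the NIR-to-white-light ratio of false-positive counts;
- a note that the five- and ten-lesion rules may add selection.

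If sensitivity or specificity is still shown, label it *among lesions flagged by at least one modality*.

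Optionally, add a supportive patient-level analysis that uses the scheduled 12-month CT and recurrence data as an imperfect reference. It should state that later disease may postdate the laparoscopy. It should also state that resection findings are not listed in Table 1 and are not available for patients treated with radiotherapy.

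The core change costs only wording: it uses lesion-level results that the protocol already records and needs no new procedure. The price is that no absolute accuracy is claimed.
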